## Abstract

**Objective:**

This protocol proposes investigating the effects of short-chain fatty acids (SCFAs)—namely acetate, propionate, and butyrate—as mediators of microbiota-gut-brain interactions on the acute stress response, eating behavior, and nutritional state in malnourished patients with anorexia nervosa (AN). SCFAs are produced by bacterial fermentation of dietary fiber in the gut and have recently been proposed as crucial mediators of the gut microbiota's effects on the host. Emerging evidence suggests that SCFAs impact human psychobiology through endocrine, neural, and immune pathways and may regulate stress responses and eating behavior.

**Method:**

We will conduct a randomized, triple-blind, placebo-controlled trial in 92 patients with AN. Patients will receive either a placebo or a mixture of SCFAs (acetate propionate, butyrate) using pH-dependent colon-delivery capsules for six weeks. This clinical trial is an add-on to the standard inpatient psychotherapeutic program focusing on nutritional rehabilitation.

**Hypotheses:**

We hypothesize that colonic SCFAs delivery will modulate neuroendocrine, cardiovascular, and subjective responses to an acute laboratory psychosocial stress task. As secondary outcome measures, we will assess alterations in restrictive eating behavior and nutritional status, as reflected by changes in body mass index. Additionally, we will explore changes in microbiota composition, gastrointestinal symptoms, eating disorder psychopathology, and related comorbidities.

**Discussion:**

The findings of this study would enhance our understanding of how gut microbiota-affiliated metabolites, particularly SCFAs, impact the stress response and eating behavior of individuals with AN. It has the potential to provide essential insights into the complex interplay between the gut, stress system, and eating behavior and facilitate new therapeutic targets for stress-related psychiatric disorders.

*This protocol is prospectively registered with ClinicalTrials.gov, with trial registration number NCT06064201.*

## Introduction

### Background

As a potent modulator of the bidirectional communication between the host's gastrointestinal tract and brain, the gut microbiota plays a central role in what's commonly known as the gut-brain axis. The gut microbiota can impact multiple bodily processes such as metabolism, immunological responses, body weight regulation, brain function, and eating behavior [1–3]. Concurrently, diet greatly influences the gut microbiota composition [4], suggesting a complex interplay. In particular, dietary fiber intake has been identified as a primary factor determining gut microbiota composition and function. Dietary fiber is considered an important substrate that helps to preserve gut ecology and regulate host physiology [5]. In patients with anorexia nervosa (AN), who characteristically maintain highly restricted diets, significant alterations in gut microbiota composition have been reported [6–9]. Moreover, shifts in the gut microbiota composition of patients with AN have been observed before and after renourishment. However, even after renourishment, the gut microbiota composition continues to differ from healthy controls [10–14]. Changes in gut microbiota composition have also been considered a potential contributing factor to gastrointestinal symptoms, such as constipation and bloating, which are frequently experienced by this patient population [15]. Current literature on nutritional rehabilitation in AN recommends energy-rich diets. Further, it proposes that these diets should be high in both fat and fiber to help establish a gut microbiome that more closely mirrors healthy individuals [16].

Short-chain fatty acids (SCFAs), metabolites produced following the bacterial fermentation of dietary fiber in the large intestine, are considered candidate mediators of the gut bacteria's effects on the host [17]. Acetate, propionate, and butyrate are the most abundant SCFAs and may affect the host through immune, endocrine, neural, and humoral pathways [18]. Stress is the physiological response to a challenging physical, emotional, or cognitive encounter that exceeds the body's coping resources and activates the sympatho-adrenal medullary pathway (SAM) and the hypothalamus–pituitary–adrenal (HPA) axis. Interestingly, recent evidence suggests that SCFAs mediate the effects of gut bacteria on stress responses of the HPA axis [19–21]. Oral supplementation of SCFAs in rodents reduced corticosteroid response to acute stress, reduced stress-induced gastrointestinal permeability, and reversed changes in anhedonia [20, 21]. Human translational research found that administering SCFAs to the large intestine attenuated the cortisol response to acute psychosocial stress [19]. While the stress response can be adaptive and beneficial, prolonged or exaggerated stress can heighten the risk of developing neuropsychiatric disorders [22]. The involvement of the HPA axis in individuals with AN has been implicated in the development and perpetuation of this disorder [23–26]. Researchers hypothesize that eating disorder-related behaviors, such as restricting, binging, purging, or excessive physical exercise, may function as dysfunctional adaptations to alleviate and manage negative affective states [27–29]. These maladaptive eating behaviors often increase in response to stress and negative emotions [30, 31]. This consequently forms a vicious cycle, where the continued physiological state of nutritional deprivation can lead to subjective and objective stress activation (e.g., via chronic HPA axis stimulation and autonomic nervous system alterations) [23, 32, 33]. The possible role that the gut microbiota and SCFAs might play in the maladaptive stress responses and related eating behaviors characteristic of AN is intriguing and presents a promising research avenue to expand our understanding of this complex disorder.

Data on SCFAs in AN is limited, but some studies have reported lower fecal concentrations of SCFAs [6, 7, 13, 34, 35]. One study examined fecal SCFAs in patients with AN and observed their nutritional intake. They found that individuals with AN had lower fecal concentrations of butyrate and propionate, a normal protein and fiber intake, and lower carbohydrate and fat intake [35]. A systematic review of microbiological data suggests that characteristic alterations in the gut bacteria of patients with AN include a decrease in butyrate-producing species and an increase in species that degrade mucin, which increases gastrointestinal permeability [9]. However, current findings on fecal short-chain fatty acid (SCFAs) concentrations in AN are inconclusive, as fecal SCFAs only provide information on non-absorbed SCFAs and do not reflect in situ production rates, absorption, or interactions with other biologically relevant molecules or cell types. A cross-sectional study on serum SCFAs found significantly lower levels of butyric, isobutyric, and isovaleric acid in individuals with active and recovered AN [36]. Despite a growing body of evidence indicating a relationship between the gut microbiota and AN, there is a significant gap in research that causally examines the role of SCFAs and explores the interactions between the gut microbiota, SCFAs, stress response, and eating behavior in AN.

### Study aims

Building on the current gaps in the literature, we designed a triple-blind, randomized, placebo-controlled trial to examine the role of SCFAs as mediators of microbiota-gut-brain interactions in AN. Specifically, we aim to assess the effects of SCFAs on the acute stress response, eating behavior, and nutritional status in patients with AN following SCFA delivery to the large intestine using pH-dependent colon-delivery capsules (CDCs). This method allows the administration of SCFAs in exact amounts in a chronically tolerable manner while mimicking, as closely as possible, the process of bacterial fermentation of dietary fiber in the gut. We hypothesize that colonic SCFA administration daily for six weeks will modulate neuroendocrine [cortisol, adrenocorticotropin hormone (ACTH), salivary-alpha amylase], cardiovascular (heart rate, heart rate variability), and emotional responses (subjective stress, anxiety, perceived control, hunger and desire to eat) to acute laboratory stress. Additionally, we predict that the intervention will result in a shift in dietary choices towards less restricted choices, as captured during a food choice task (FCT), and an improvement in the nutritional state, reflected by a greater increase in BMI.

The longitudinal design of this study provides a unique opportunity to examine the causal role of SCFAs in stress and eating behaviors in individuals with AN. By stepping away from the typical cross-sectional studies in the gut microbiota research field, our work can yield new insights into the complex interplay between the gut, stress system, and eating behavior and facilitate new therapeutic targets for stress-related psychiatric disorders.

## Methods

The Standard Protocol Items: Recommendations for Interventional Trials (SPIRIT) checklist [37] was used as a guideline for this protocol.

### Study design and setting

This study is a monocentric, randomized, triple-blind, placebo-controlled trial with two parallel arms. Participants in both groups will receive concomitant treatment as usual, consisting of an inpatient psychotherapeutic program of 12 weeks focusing on nutritional rehabilitation. Using a block randomization method, we will randomly assign participants to the placebo or SCFA group with a 1:1 allocation ratio. The total duration of the study is 12 weeks, including a pre-intervention baseline visit, which takes place within the first week of hospitalization, a post-intervention visit at six weeks, and a follow-up visit at 12 weeks. The study will be conducted at the Leuven University Psychiatric Hospital (UPC Z.Org), Belgium.

### Sample size

Based on our previous work [19], we calculated, using the General Linear Multivariate Model Power and Sample Size software (GLIMMPSE), that a total sample size of 70 participants (n = 35 per treatment arm) yields sufficient power (80%) to detect the previously found effect of SCFAs on the cortisol response to an acute stress paradigm. Given that no information is available to calculate the effects of SCFAs on stress-induced cortisol response in patients with AN where greater variability might be present, we increased the sample size to 80 participants (n = 40 per arm). Based on a sensitivity power calculation (G*Power 3.1.9.2 software), 40 participants per arm would enable us to achieve 80% power to detect a small effect (Cohen's f = 0.16) in a within-between 2 (“visit”, baseline vs. post-intervention) × 2 (“treatment”, placebo vs. SCFA) mixed ANOVA model. Taking into consideration a 15% risk of dropout, we aim to recruit 92 individuals in total.

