### Statistical analysis

#### Statistical methods for primary and secondary outcomes

The primary and secondary outcome variables will be analyzed using linear mixed models with “group” (placebo or SCFAs) as a between-subject factor and “visit” (pre- or postintervention) and, where appropriate, “timepoint” (measurement point within each visit) as within-subject factors. The group-by-visit and the group-by-visit-by-timepoint interaction effects constitute the principal effects of interest. If participants fail to exhibit an elevated cortisol stress response following stress induction, we will exclude their data from the analysis. To investigate the effect of the SCFAs intervention on treatment response, we will further control for BMI by including changes in BMI between visits 1, 2, and 3 in the linear mixed model as a continuous covariate. To investigate whether the changes in circulating SCFAs levels are mediated by the changes in the cortisol stress response to our stressor, we will pool all stress responders and enter the change in SCFA levels (post-intervention—pre-intervention) into the linear mixed model as a continuous covariate, including its interaction with visit, while omitting the group variable. The chosen significance level is alpha = 0.05. Follow-up planned contrasts will be conducted if there is a significant interaction effect and will be corrected for multiple testing comparisons using step-down Bonferroni (Holm) adjustment. Data of the intervention group will be further exploratively analyzed using linear mixed models with restrictive type AN and binge/purge type AN as “patient group,” investigating differences between the intervention of SCFAs between subtypes of patients with AN. In addition, we will enter the changes in questionnaires (baseline, post-intervention) into a linear mixed model as continuous covariates to investigate in an explorative way whether these changes (e.g., in AN severity, affect changes, subjective stress, etc.) are mediated by the changes in SCFAs levels and microbiota composition.

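### Recruiting 92 covers 13% dropout rather than 15%, and the sample size makes no allowance for the planned exclusion of cortisol non-responders

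*Protocol article*

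**What the plan says.** The Sample size section of the protocol article builds the number in three steps.

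- A GLIMMPSE calculation based on the group's earlier work gives 70 patients (35 per arm) for 80% power to detect the cortisol effect found there.
- The target is raised to 80 (40 per arm) because variability may be greater in anorexia nervosa. A G*Power sensitivity calculation for a 2 × 2 visit-by-treatment mixed ANOVA is then reported: "40 participants per arm would enable us to achieve 80% power to detect a small effect", given as Cohen's f = 0.16.
- Losses are added: "Taking into consideration a 15% risk of dropout, we aim to recruit 92 individuals in total".

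Dropout is the only loss named. In the section on statistical methods for primary and secondary outcomes, the rule for participants who do not show an elevated cortisol response after stress induction is: "we will exclude their data from the analysis". The Outcomes section names the salivary cortisol response as the primary outcome, so this rule acts on the primary analysis. The methods section also fixes the test level: "The chosen significance level is alpha = 0.05".

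**The concern.** There are two gaps between the number recruited and the number on which the power statement rests, and one point of wording.

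First, a dropout allowance should divide the evaluable number by the proportion retained. Multiplying by one plus the dropout rate gives too few.

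Second, and of more weight, the 80 patients behind the stated power are treated as the analysed number, yet another section of the same article takes some of them out of the analysis. The increase from 70 to 80 does not fill this gap, because its stated reason is variability.

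Third, the word small describes the effect on the f scale without saying what difference between arms it represents.

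At stake is whether readers of the results can rely on the stated power for the primary outcome.

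**Working it through.** **Inputs from the protocol article.** Evaluable target 80 (40 per arm); f = 0.16 at 80% power; dropout 15%; 92 recruited (all Sample size). Allocation 1:1 (Study design and setting). Alpha 0.05 (statistical methods).

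**Assumptions, because the article gives no value.** Correlation between visits ρ = 0.5. Cortisol non-response 10% to 30%. f = 0.16 unchanged by the exclusion.

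**1. Reproducing the stated sensitivity.** For the interaction in a 2 × 2 within-between design, the noncentrality is λ = f² × N × m/(1 − ρ), with m = 2 visits and an F test on (1, N − 2) degrees of freedom.

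- N = 80, f = 0.16, ρ = 0.5: λ = 0.0256 × 80 × 2/0.5 = 8.19, power 80.7%.
- Solving for exactly 80% power gives f = 0.159.

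The stated f = 0.16 therefore reproduces. This covers the group-by-visit contrast only. The GLIMMPSE figure of 70 cannot be recomputed, because its inputs are not in the article.

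**2. Dropout.**

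- 80 × 1.15 = 92, the stated figure.
- 92 × 0.85 = 78.2 remaining.
- 80/0.85 = 94.1, so 95, or 96 (48 per arm) for equal arms.
- 1 − 80/92 = 13.0%, the dropout that 92 can absorb.
- Power at N = 78, f = 0.16, ρ = 0.5: λ = 0.0256 × 78 × 2/0.5 = 7.99, power 79.7%.

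**3. Exclusion of non-responders after 15% dropout.** N analysed = 78.2 × (1 − non-response rate).

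| Assumed non-response | N analysed | Power at f = 0.16 |
|---|---|---|
| 10% | 70.4 | 75% |
| 20% | 62.6 | 70% |
| 30% | 54.7 | 64% |

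A rate of 1 − 70/78.2 = 10.5% would bring the analysed number back to 70, the size before the increase made for this population.

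**4. What f = 0.16 means as a difference.** In this design the between-arm difference in change is 4f raw SDs, and the SD of the change score is √(2(1 − ρ)) raw SDs.

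- At exactly 80% power with 40 per arm and ρ = 0.5: 4 × 0.1586 = 0.634 raw SD. The rounded f = 0.16 gives 0.64.
- In SDs of the change score, the difference detectable with 80% power is 0.634 at every correlation.
- In raw SDs it is 0.90 at ρ = 0, 0.63 at ρ = 0.5 and 0.40 at ρ = 0.8.

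**The case against.** The sensitivity statement is conditional on 40 per arm, and on that condition it is right. The dropout slip costs about one point of power, and 78 is still more than the 70 that the article gives as sufficient for the earlier cortisol effect. All of this stands, and the slip would not merit comment alone.

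The losses from exclusion rest on rates that appear nowhere in the article and on an effect held constant. Removing non-responders can change both the mean effect and its variance. If f among those kept were 15% larger, power with about 63 patients would be roughly 82%. So the direction of the power change is not established, and whether the earlier study's input already reflected responders only cannot be seen. This stands too. It does not remove the mismatch: the number behind the stated power is not the number to be analysed.

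On wording, the article prints the metric and its value, and on the conventional f scale (0.10 small, 0.25 medium) 0.16 lies nearer to small. A reader might infer that the effect is mislabelled and is really above medium. That follows only by moving to another scale with other benchmarks, so the point is one of clarity. A reader might also infer that a null result is meant to rule out small effects. The article makes no such claim; it bases its number on the previously found effect.

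Patients discontinued for poor capsule adherence may be meant to fall within the 15%, so they are not counted here as a further loss.

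**Conclusion.** The point holds in a limited form. The dropout allowance is computed the wrong way: 92 covers 13.0% loss, and 15% leaves about 78. This is arithmetic on the article's own figures, and its effect on power is minor (80.7% to 79.7% at f = 0.16, assuming ρ = 0.5).

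The more important part is the uncounted exclusion. Two sections of the article do not fit together: one powers the trial on 80 evaluable patients, the other removes some of them from the primary analysis. The size is unknown. About 75% to 64% power at 10% to 30% non-response is an illustration that depends on the assumed rates and on an unchanged effect.

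A reader might conclude that the power calculation is wrong or that the trial is shown to be underpowered. The document supports neither: the calculation reproduces, and no non-response rate is given. The description of the effect as small needs clarification only.

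**What to change.** No additional enrolment is required.

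- **Sample size, dropout.** State that 92 randomised allows for 13% dropout, and that at 15% about 78 are expected, with power just under 80% at f = 0.16 and an assumed correlation of 0.5 between visits.
- **Statistical methods, exclusion.** Keep all randomised patients with cortisol data in the primary analysis and make the responder-only analysis a sensitivity analysis. If the exclusion stays in the primary analysis, state the power after it, with the assumed non-response rate.
- **Sample size, effect.** Beside f = 0.16, report that 40 per arm gives 80% power for a between-arm difference in change of about 0.63 SD of the change score, which equals raw SD only if the correlation is 0.5. Drop the word small.

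The cost is one reworded paragraph and one changed sentence in the methods. The stated figures become slightly less favourable. Moving the responder-only analysis also changes the primary analysis set, so it should be fixed before unblinding.

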### Eligibility criteria

Females of at least 16 years of age, diagnosed with AN per DSM-5 guidelines—having first met these DSM-5 criteria less than seven years ago—and having a current Body Mass Index (BMI) of less than 17.5 kg/m^2^ will be recruited. Further, participants must be Dutch-speaking and agree to participate in the inpatient therapeutic program on the specialized eating disorder unit of the hospital. Regarding the exclusion criteria, we consider several factors that potentially impact the stress task used in the study. These include substance or alcohol abuse, chronic use of sedatives or sleep medication, and a high caffeine intake, defined as more than 1000 ml of coffee daily or equivalent quantities of other caffeine-containing substances. Moreover, we will exclude individuals with medical or psychiatric conditions that may interfere with study procedures or risk patient well-being. Medical criteria for exclusion encompass gastrointestinal issues like Crohn's disease and ulcerative colitis, as well as individuals who are medically unstable due to severe malnutrition. Regarding psychiatric exclusions, individuals experiencing acute suicidal thoughts or behaviors are not eligible to participate. Additional exclusion factors relate to their potential impact on the microbiota composition. These include recent use of pre- or probiotics (within the last month before the study), use of antibiotics (within the previous three months before the study), and use of antipsychotics. However, other drugs will be permitted if the patients have been on a stable dosage for at least four weeks.

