## Outcomes

### Primary and secondary outcomes

The primary outcome of this study focuses on the salivary cortisol response to acute laboratory stress. We will examine the change in cortisol levels within and between SCFAs and placebo groups. Crucial secondary outcomes encompass the participants' food choices and nutritional status (BMI). All other measures delineated in the subsequent sections serve as secondary outcome measures. See Table 1 for an overview of scheduled assessments.

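### The eligibility criteria aim to remove factors that affect the stress task, yet their stable-dose permission, as written, admits users of glucocorticoids (primary cortisol outcome) and beta-blockers (secondary heart-rate and amylase outcomes)

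*Protocol article*

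**What the plan says.** The Eligibility criteria section gives a reason for its first group of exclusions: "Regarding the exclusion criteria, we consider several factors that potentially impact the stress task used in the study". It then names them: "These include substance or alcohol abuse, chronic use of sedatives or sleep medication, and a high caffeine intake". A further group is justified by effects on the microbiota. It covers pre- and probiotics and "use of antibiotics (within the previous three months before the study), and use of antipsychotics". A general clause addresses illness: "we will exclude individuals with medical or psychiatric conditions that may interfere with study procedures or risk patient well-being". The section ends: "However, other drugs will be permitted if the patients have been on a stable dosage for at least four weeks".

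On outcomes, the Primary and secondary outcomes section states: "The primary outcome of this study focuses on the salivary cortisol response to acute laboratory stress". The Study aims section also hypothesises changes in ACTH, salivary alpha-amylase and "cardiovascular (heart rate, heart rate variability), and emotional responses"; these are secondary outcomes. The Neuroendocrine measures section says that samples are analysed by ELISA, and that menstrual phase and hormonal contraceptive use are noted because of their effect on cortisol.

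Medication is recorded before and throughout the study (Other measures and questionnaires), and its use does not end the trial intervention (Interventions and concomitant care). Randomisation is not stratified. The Statistical analysis section removes participants who show no cortisol rise after stress induction.

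**The concern.** The section's purpose and its closing sentence pull in different directions. A heavy coffee drinker is screened out to protect the stress task. A patient on a stable glucocorticoid is let in, although that drug class acts on the same axis as the primary outcome. It can suppress the HPA response, and some of these compounds may be read as cortisol by an immunoassay. Beta-blockers raise a similar but smaller problem: they act on heart rate and alpha-amylase, which are secondary.

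Requiring four weeks at a stable dose guards against a change in drug effect between visits. It does not bring back a response that is suppressed at both visits. Such a patient takes a randomised place and undergoes two stress tests. The patient then either contributes little information on the arm difference or is removed after randomisation as a non-responder, although the admission medication history would have identified the drug beforehand. At stake are some power and a slightly larger post-randomisation exclusion.

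**Working it through.** **Text check.** Set side by side, the provisions in Eligibility criteria work as follows:
- Stress-task exclusions: substance or alcohol abuse, chronic sedatives or sleep medication, high caffeine. No glucocorticoid or beta-blocker.
- Microbiota exclusions: pre-/probiotics, antibiotics, antipsychotics. Again neither class.
- Interfering-conditions clause: concerns diseases, and names no drug.
- Closing sentence: permits other drugs, with dose stability as the only condition.

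Neither class appears elsewhere in the article. The analysis described there has no term for medication.

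**Reproducing the plan's power figure.** Inputs from Sample size and Statistical analysis: N = 80 (40 per arm), Cohen's f = 0.16, m = 2 visits, alpha = 0.05, stated power 80%. The correlation rho between visits is not given; 0.5 is assumed. For the within-between interaction, with 1 and N − 2 degrees of freedom:

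lambda = f² × N × m / (1 − rho) = 0.0256 × 80 × 2 / 0.5 = 8.192, which gives power 80.7%.

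This matches the stated 80%. Other values of rho do not: 51.6% at 0, 66.6% at 0.3, 95.4% at 0.7. So 0.5 is a reasonable working value.

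**Illustration of the cost.** Let q be the share of analysed patients whose cortisol response is fully blunted by a drug. The article gives no q, so a range is shown.
- Kept in the analysis: the effect becomes f × (1 − q), with the residual variance taken as unchanged. At q = 5%, f = 0.152 and lambda = 0.023104 × 80 × 2 / 0.5 = 7.39.
- Dropped as non-responders: N becomes 80 × (1 − q). At q = 5%, N = 76 and lambda = 0.0256 × 76 × 2 / 0.5 = 7.78.

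| q | Power if kept | Power if dropped (N) |
|---|---|---|
| 0% | 80.7% | 80.7% (80) |
| 2% | 79.1% | 79.7% (78) |
| 5% | 76.6% | 78.6% (76) |
| 10% | 72.0% | 76.4% (72) |
| 20% | 61.8% | 71.2% (64) |

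The calculation concerns glucocorticoid users and cortisol only. Beta-blocker users do not enter it, because the concern about them is confined to heart rate and alpha-amylase. Full blunting is an upper bound: some users, particularly of inhaled products, will keep part of their response.

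**The case against.** **The lists may be illustrative.** The exclusions are introduced as examples, and a journal article condenses the full protocol, which may itemise prohibited drugs. This would carry weight if the article were merely silent. It is not: the last sentence positively permits other drugs on one condition, and a full protocol that excluded these two classes would not agree with it. The point weakens any claim about who will actually be enrolled, but not the claim about what the text allows.

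**Other clauses catch some of these patients.** A reader might infer that the stable-dose sentence overrides the interfering-conditions exclusion. It does not; both apply. Crohn's disease and ulcerative colitis are excluded by name, and the investigator's final eligibility check may exclude others through their underlying disease. That protection is partial, because it depends on judgement and mentions no drug.

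**Recording may suffice.** The protocol records hormonal contraceptives rather than excluding their users, and it records all medication. A covariate or sensitivity analysis could follow and may properly be left to an analysis plan. This stands as an answer for beta-blockers and secondary outcomes. It is weaker for glucocorticoids, because adjustment cannot recover a response that was never produced.

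**Bias.** A reader might infer that the trial's comparison would be biased. The documents do not support that. Allocation is random, the dose must be stable, and the effect of interest is group by visit, so such a drug acts at both visits in either arm. What remains is dilution, noise and, without stratification, chance imbalance of a few users. The rule that removes non-responders has problems of its own, which should not be charged to this sentence.

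**Conclusion.** The point holds in a limited form. The closing permission in Eligibility criteria is inconsistent with that section's own stress-task rationale and, as written, admits users of glucocorticoids, which bear on the primary outcome, and of beta-blockers, which bear only on secondary ones. The later steps do not make good the loss. The medication record has no stated use in the analysis, and removing non-responders acts after randomisation and does nothing for heart rate.

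The size is probably modest. At an assumed 5% share with full blunting and rho = 0.5, power drops by about 4 points (80.7% to 76.6%) if these patients are kept, or about 2 points (to 78.6%) if they are dropped. The real share is unknown and may be small in young female inpatients. The pharmacological effects are general knowledge, not figures from the article, and whether a given steroid cross-reacts depends on the compound and the kit.

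A reader might go further and conclude that every user of either class is lost to the primary outcome. The article does not support this: beta-blocker users can still contribute a cortisol response, and not every glucocorticoid user will be fully blunted.

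**What to change.** Reconcile the stable-dose permission with the stress-task rationale by amending one line of Eligibility criteria:
- Limit the permission to drugs that do not act directly on the HPA axis, and list glucocorticoid use among the stress-task exclusions. Leave the exact products, routes and look-back period to the investigators. Hormonal contraceptives, which the protocol has chosen to record, can stay as they are if the line says so.
- For beta-blockers, either exclude users in the same way or state in advance that users will be omitted from the heart-rate and alpha-amylase analyses. Define use from the baseline medication record, so that the omission depends only on a pre-randomisation fact and leaves the cortisol analysis untouched.

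The cost is one amendment, with no new data collection because medication is already recorded. The downside is the loss of a few screened patients in a single-centre trial and slightly narrower generalisability. If patients have already been enrolled under the current wording, the baseline record allows a pre-specified sensitivity analysis without glucocorticoid users.
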